
**Figure 2 fig2:**
[figure not shown]
Complete phase I protocol showing the three controlled environment simulations (i.e., commute by motorized-vehicle [from phase 2 to phase 2.2], walking [from phase 3 to phase 3.2], and cycling [from phase 4 to phase 4.1]).

In the Phase II, the procedures of the intervention will be tested as a pilot phase to ensure its feasibility and effectiveness. Prior to this, the research team will undergo joint training for internal evaluation. The pilot phase will be implemented in adolescents from a school in Granada over 2 days, with the involvement of the entire research team, lasting approximately 1 h per day. In this pilot phase, the organization of evaluations and the effectiveness of the tests used will be observed by the research group. Moreover, the school-based cycling intervention, which will be described in detail later, will be designed by research personnel trained as Physical Education teachers and graduated in Sport Sciences, and subsequently reviewed by research experts. During the baseline and follow-up of Phase II, the RMR, along with various health-related outcomes, will be assessed. These include individual, social, environmental, and safety factors associated with ACS (see Table 3). Figure 3 outlines the assessments to be conducted during the baseline and follow-up periods.

**Table 3 tab3:** Summary of the variables and instruments phase I and PHASE II.

Section	Variables	Instrument	Phase I	Phase II
Primary outcomes				
Physiological outcomes	Resting metabolic rate	Omnical (Maastricht Instruments, Maastricht, The Netherlands)		X
	Energy expenditure	Cosmed K5 (Cosmed, Rome, Italy)	X	X
Secondary outcomes				
Socio-demographic characteristics	*Students:* Age, school grade and class, gender, full postal address, bicycle owners	Student questionnaire	X	X
	*Parents:* School, name, age, gender, children’s gender, and full postal address, parental education level	Family questionnaire		X
Physiological outcomes	Blood Pressure	Stethoscope		X
	Heart rate	Polar Ignite 10, chest band and watch (Polar Electro Oy, Kempele, Finland)	X	X
	Body temperature	Ibuttons (Maxim/Dallas Semiconductor Corp., USA)	X	X
Physical outcomes	*Physical activity levels*	Accelerometer ActigraphGT3x+	X	X
		Youth Activity Profile questionnaire (YAP)		X
	*Physical fitness* Cardiorespiratory capacity			X
	Muscular strength	Course Navette		X
	Physical literacy	Analog dynamometer		X
		Spanish perceived physical literacy instrument for adolescents (PPLI- Q) and Bruininks-Oseretsky Test of Motor Proficiency (BOT-2)	X	X
	*Anthropometric measures* Body mass	Weighting platform (Seca 876, Seca, Ltd., Hamburg, Germany)	X	X
	Height	Height meter (Seca 2013, Seca, Ltd., Hamburg, Germany)	X	X
	Waist and neck circumferences	Non-elastic tape measure	X	X
	*Body composition* Fat free mass, fat mass, lean mass index, fat mass index, body fat percentage, visceral adipose tissue, and bone mineral content	Dual energy X-rayabsorptimetry (DEXA)	X	X
Psychosocial outcomes	Perceived barriers to active commute to school	Barriers for active commuting to school questionnaire (BATACE) and Parental Perception of Barriers toward Active Commuting to School (PABACS)		X
	Autonomy, competence, and relatedness	Basic Psychological Need Satisfaction Need in Active Commuting to and from School questionnaire (BPNS ACS) and Behavioral Regulation in Active Commuting to and from School (BR-ACS)		X
	Satisfaction and motivation in ACS	Positive and Negative Affect Schedule (PANAS) and Rosenberg Self-Esteem Scale (RSES)		X
Other relevant outcomes	*ACS and related outcomes* Usual mode of commuting, frequency of trips to and from school, and independent mobility	PACO questionnaire		X
	Cycling knowledge and cycling skills	Cycling tests		X
	*Family socioeconomic status* Family income	Family Affluence Scale questionnaire (FAS III)		X
	*Parental perceptions* Barriers to allow their adolescent to active commuting to/from school	Parental Perception of Barriers toward active commuting to school questionnaire (PABACS)		X
	Distance home-school	Google Maps and GPS		X
	Trips to and from school characteristics (i.e., distance, speed, and duration)	GPS	X	
	*Weather* Temperature during commuting simulations	iButtons (Maxim/Dallas Semiconductor Corp., USA)	X	
	Temperature (maximum, minimum, mean), total rainfall, and mean wind speed	NationalWeather Data Bank		X
	*School characteristics* Student enrolment, socioeconomic status, and school engagement	Electronic and manual Search, Geographical Information System. Ministry of Education and Vocational Training.		X

ACS, active commuting to and from school; GPS, Global Positioning System.

**Figure 3 fig3:**
[figure not shown]
Intervention design phase II of the ENERGYCO study.

Assessment day 1 (2): this session will include anthropometry, blood pressure, muscular strength, and motor competence assessment at an indoor sport facility.

Assessment day 2 (2 h): in this session the cardiorespiratory fitness of the participants will be assessed. Once participants have finished the test, they will have to complete an online student-questionnaire. During this session, participants will receive a belt with an accelerometer (GT3X+ accelerometers; ActiGraph, Pensacola, FL) and a Global Positioning System (GPS; QStarz BT-Q1000XT; Travel Recorder, International Co, Ltd. Taipei, Taiwan), a heart rate monitor, including chest band and watch, (Polar Ignite 10, Polar Electro Oy, Kempele, Finland) for measuring their resting heart rate during the first weekend of the baseline week, and to use it during the cycling trips to and from school.

Assessment day 3 (1 h and a half): in this session the RMR of the participants will be assessed. Participants will have to come to the indicated facility in a postabsorptive state (10–12 h without consumption of caloric food or beverages) and by passive transport. Moreover, participants from the experimental group will be provided with two links, one to fill in weekly, after the *Bikeability* sessions week, providing information about their weekly cycling experience to and from school and their opinions on the motivational strategies, and another link with access to a questionnaire to be filled in by their parents.

### Outcome measures

2.7

#### Primary outcomes

2.7.1

##### Resting metabolic rate

2.7.1.1

RER will be measured using the Omnical metabolic cart (Maastricht Instruments, Maastricht, The Netherlands), a validated system for assessing volumes of oxygen consumption (VO_2_) and carbon dioxide production (VCO_2_) during resting conditions which a low measurement error for determining RER (1.7 ± 0.9%) (54). During the test, a ventilated plastic canopy will be connected to the instrument and placed over the participant, allowing the individual to breathe normally while the Omnical records CO_2_ and O_2_ levels in inhaled and exhaled air every 5 s. The device will be calibrated daily using a gas mixture of 18.0% O_2_ and 0.8% CO_2_. Data will be analyzed as the average VO_2_ (ml/min) and VCO_2_ (ml/min) over a 10-min stable period, aggregated by participant at baseline and follow-up. However, since the RMR measurement can only be performed at the research center in one of the participating cities, a contingency plan has been established in case participants from other cities cannot travel to the evaluation center. In such cases, the RMR will also be estimated for all participants using the Schmelze equation, which has demonstrated superior results compared to the gold standard among 12 equations, including a low measurement difference with the gold standard (−51.0 to 15.0 kcal/day), low % bias (−1.6 to 5.8%), an acceptable prediction percentage relative to the gold standard (40.7 to 59.0%), and a low RMSE (136.2 to 305.4 kcal/day) for adolescents with normal weight, overweight, or obesity (55).

##### Energy expenditure related to active commuting to school

2.7.1.2

PAEE related to different modes of commuting to school (i.e., walking, cycling, passive modes) will be measured using the Cosmed K5 portable metabolic system in Phase I. The Cosmed K5 has previously shown a good level of agreement compared to stationary metabolic carts at low cycling intensity (5.8% difference in VO_2_). At moderate intensities, it slightly underestimated VO_2_, VCO_2_, and energy expenditure (~6.6–6.9%). Additionally, during walking tests, the Cosmed K5 demonstrated high reproducibility, with a coefficient of variation of 4.5% for energy expenditure per kilometer and a concordance coefficient of 0.91. VO_2_ measurements were consistent, with low variability in the fraction of expired oxygen (coefficient of variation of 0.9%) (56). The Cosmed K5 is worn on the back with a harness and measures oxygen consumption (VO_2_) and carbon dioxide production (VCO_2_) in breath-by-breath mode. Before each assessment, the device will be calibrated using a reference gas mixture of 15.92% O_2_ and 5.03% CO_2_. Delay calibration for the breath-by-breath mode will also be performed (57). During the test, participants will breathe normally while commuting, and the Cosmed K5 will record data continuously. Data will be analyzed as the mean VO_2_ and VCO_2_ (ml/min) during each commuting mode. In Phase II, PAEE related to cycling will be estimated using predictive equations developed in Phase I. These equations will incorporate variables such as distance, speed, and heart rate, and will be cross-validated against PAEE measurements obtained with the Cosmed K5 to ensure accuracy. Therefore, data will be analyzed as the mean VO_2_ and VCO_2_ (ml/min) during each cycling trip to and from school, aggregated by participant during the intervention period.

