## Introduction

1

Resting metabolic rate (RMR) constitutes the primary component of 24-h energy expenditure, representing the energy requirement for sustaining bodily functions while at rest in thermoneutral conditions (1). Given, fat-free mass (FFM) serves as a robust predictor of RMR in adolescent population (2, 3), exercise-induced weight loss is an important research topic since it leads to increases RMR by increasing the fat free mass component (4). However, studies in the adolescent population to modify the RMR have focused mainly on resistance or aerobic exercise (5, 6), without taking into account how regular physical activity (PA) might affect the RMR. Understanding PA energy expenditure (hereinafter referred to as PAEE) as the result of any muscular movement due to PA (7), the interaction of intensity, duration, and frequency of PA determines the total PAEE. In that sense, the American College of Sports Medicine states that exercise and health-oriented PA should be performed consistently to obtain its associated benefits. Nevertheless, nowadays there is an energy imbalance in the youth population, with high energy intake and low PAEE (8). This fact may have led to an increase in obesity in the young population worldwide, by 5.6% in girls and 7.8% in boys between 1975 and 2016 (9). In fact, the World Health Organization (WHO) has considered the overweight and obesity as a global public health concern (10). Although overweight and obesity have a multifactorial origin (9, 11), the literature recommends increasing PAEE through regular PA, as it is the most easily modifiable component of 24-h energy expenditure (11), to address the current situation. Therefore, interventions targeting young populations should aim to increase PAEE to restore or maintain energy balance (12).

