
Furthermore, ACS interventions have primarily been conducted in children (i.e., from 6 to 11 years) rather than in adolescents (i.e., from 12 to 17 years) as well as promoting walking rather than cycling. These interventions have primarily focused on changes in the mode of commuting, frequency of commuting, or increased PA levels (36–39) rather than assessing the effects on 24-h energy expenditure components (i.e., RMR and PAEE). In addition, interventions to improve RMR or PAEE have mainly consisted of resistance or endurance trainings (5, 11), being these activities performed out of school. To the best of our knowledge the effect of a school-based cycling intervention on the RMR and daily PAEE of adolescents has not been studied to date. In fact, the assessment of the effects of a school-based cycling intervention could be particularly important to consider as a suitable strategy to increase the RMR and re-balance PAEE in the adolescent population. In addition, a school-based cycling intervention will not only produce effects at physiological level (i.e., RMR or PAEE), but it will also allow to deepen the effects of this mode of commuting to school at physical or psychosocial level in the adolescent population. It has been shown that cycling to school is associated with greater grip strength and vertical jump (40), but the association does not imply causality. Similar results occur at the psychosocial level, where cycling to school has been associated with greater well-being or increased social relations compared to use passive passively commuting to school in adolescents (41). Moreover, there is controversy as to whether cycling to school could improve young people’s body composition (14). Thus, a school-based cycling intervention is needed to increase and improve the evidence of the effects of cycling to school in physiological, physical, and psychosocial outcomes.

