#### Study assessment protocol

2.6.1

In Phase I, participants will perform three different simulations (i.e., commute by motorized-vehicle, walking, and cycling [see Figure 2]): (1) a simulation of driving to school will be performed by motorized-vehicle. After all the calibration process of the Cosmed K5 (both, flow and gas analyzers will be calibrated before every gas exchange measurement), a face-mask attached to the K5 will be place and gas exchange will be check during a two-minute period before the measurement start. After the check phase, gas exchange recording start during a five-minute period, while participants remain seated. Then, the participants will simulate commute in a motorized-vehicle by remaining seated in a chair for another 15-minute period, having previously walked for 2 mins simulating that participants are moving toward the motorized-vehicle from home. After this first simulation, there will be a five-minute period of cooling down. The total time of this first test will be 27 min. (2) A simulation walking to school will be conducted in a closed circuit defined by the research staff. The same procedures mentioned before will be followed. Then, the participant will walk for 15 min (the participant will determine the speed and intensity of walking) and finish with a five-minute cool down; (3) Participants will simulate a cycling route. They will wait for five-minute after walking and they will start cycling during 15-minute period along the designated route. The simulation will finish with a five-minute cool down period. The total time used in the walking and cycling simulations will be 45 min. These times were chosen because an average walking speed of 4.4–4.6 km/h would not exceed the distance Spanish adolescents are willing to walk to their educational center (1,350 m) (52). While no study in Spanish adolescents indicates the distance, they are willing to cycle to school, we estimated a distance of 4,200 m, the threshold distance used for Australian adolescents (53), with which a speed of approximately 15 km/h would not exceed 15 min. Detailed visual information on the evaluation and calibration process of the Cosmed K5 (Cosmed, Rome, Italy) can be found at the following link.^1^ In order that one active mode of commuting (e.g., walking) does not affect the post exercise oxygen consumption, thus PAEE, of the subsequent active mode of commuting (e.g., cycling), participants will alternate randomly by first performing the simulation of walking or cycling. In addition, the alternation of starting on the bike and walking will be counterbalanced by having the same number of participants starting on the bike or walking. Finally, all data will be downloaded using PC OMNIA.9 software v3.30.79 (Cosmed, Rome, Italy).

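### The primary PAEE variable is fixed as mean VO2 and VCO2 in ml/min, a rate of intensity without trip duration, so it is not the energy expenditure that the protocol defines and hypothesises about

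*Protocol article*

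**What the plan says.** Table 3 of the protocol article lists energy expenditure beside resting metabolic rate (RMR) as a primary outcome. Section 2.7.1.2 states the analysed quantity twice:

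- Phase I: "Data will be analyzed as the mean VO_2_ and VCO_2_ (ml/min) during each commuting mode".
- Phase II, where values come from equations built in Phase I: "data will be analyzed as the mean VO_2_ and VCO_2_ (ml/min) during each cycling trip to and from school, aggregated by participant" over the intervention period.

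The Introduction describes PAEE "as the result of any muscular movement due to PA" and adds that "the interaction of intensity, duration, and frequency of PA determines the total PAEE". It treats RMR and PAEE as two separate components of 24-hour expenditure, and it hypothesises that the intervention will raise both compared with control.

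Section 2.6.1 sets 15 minutes each for walking, cycling and seated motorised travel, the last after a 2-minute walk. It also describes a resting record: "gas exchange recording start during a five-minute period, while participants remain seated". The article does not say how this record is used.

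**The concern.** A mean in ml/min carries intensity only. It has no duration and, if averaged over trips, no frequency. As written it is not energy, and nothing removes resting metabolism, which is the other primary outcome.

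The Phase II intervention asks pupils to cycle on at least 3 days a week, so it acts largely through the number and length of trips. A per-trip rate can stay flat while the energy spent commuting rises, so it cannot test the hypothesis of increased PAEE. In Phase I, a per-minute result could be read as the energy cost of a commute, although the two active modes take very different times over the same route. The unit also carries forward, because Phase II inherits the dependent variable of the Phase I equation.

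**Working it through.** The plan gives no figure for this point to reproduce. The checks below use its own speeds, times and distances.

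**Inputs from the protocol article.** Walking 4.4–4.6 km/h, cycling about 15 km/h, 15 minutes per simulation, distances of 1,350 m on foot and 4,200 m by bicycle (section 2.6.1). Per-protocol cycling to and/or from school on at least 3 days a week for 8 weeks (section 2.10.1).

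**Assumptions.** A 5-day school week. For illustration only, rest at 3.5, 4.5 or 5.5, walking at 11, 13 or 15 and cycling at 16, 20 or 25 ml/kg/min, which makes 27 combinations.

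**Formula.** Net cost per trip is proportional to (VO2 − rest) × time, with time = distance / speed.

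1. *Equal time (Phase I as designed).* The same rest value is subtracted from both modes and both are multiplied by 15, so the order of walking and cycling cannot change. It is unchanged in all 27 combinations.

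2. *Equal distance.* Walking time / cycling time = 15/4.6 = 3.26, 15/4.5 = 3.33 and 15/4.4 = 3.41. This ratio is also the break-even: cycling costs more per trip only if its net rate exceeds the walking rate by that factor. For 1,350 m, walking at 4.5 km/h takes 1.35/4.5 × 60 = 18.0 min and cycling takes 1.35/15 × 60 = 5.4 min. With rest 4.5, walking 13 and cycling 20, the net costs are 8.5 × 18.0 = 153 and 15.5 × 5.4 = 84 ml/kg, a ratio of 0.55, although cycling is higher per minute (20 against 13). Over the 27 combinations the cycling/walking ratio runs from 0.33 to 1.06 and is below 1 in 26.

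3. *Each mode at its own distance.* Walking 1,350 m at 4.5 km/h takes 18.0 min and cycling 4,200 m takes 4.2/15 × 60 = 16.8 min. Break-even is 18.0/16.8 = 1.07. No combination reverses at 4.5 km/h, though the closest is near a tie (207 against 210 ml/kg). As an aside, 16.8 min does not agree with the statement in section 2.6.1 that this ride stays within 15 min. That does not affect the present point.

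4. *Effect of leaving rest in.* Take seated travel as rest and the walk to the vehicle at the walking rate. The motorised mean over 17 min is then (2 × walking + 15 × rest)/17. Net of rest, walking / motorised = 17/2 = 8.5 whatever the values. Without subtraction the ratio is 1.8 to 3.1. The order is the same, but the size of the contrast is very different.

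5. *Phase II trips.* Three days one way: 8 × 3 × 1 = 24. Three days both ways: 8 × 3 × 2 = 48. Five days both ways: 8 × 5 × 2 = 80. Then 80/48 = 1.67 and 80/24 = 3.33. With trips of equal length and intensity the predicted rate is the same on every trip, so a participant mean is the same for 24 and for 80. A sum of rates would follow the number of trips but still omit their duration.

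**The case against.** The strongest reply has four parts.

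- *Ranking.* A reader might infer that Phase I will put the modes in the wrong order. The documents do not support that. Equal 15-minute bouts keep the order, subtracting rest cannot reverse it, and no section names energy over a common distance as the target. This part stands. What remains is a limit on interpretation: a per-minute result is not energy per commute.
- *Resting metabolism.* A reader might take it as settled that the values are gross. The text never says so, a seated record exists, and section 2.7.1.1 uses almost the same ml/min wording for RMR while discussing accuracy in kcal/day, so the sentence may be shorthand. This stands in part: the article states a plain mean and no subtraction, and no more can be claimed.
- *Trip data.* The equations include distance, speed and heart rate, section 2.10.2 compares walking and cycling by speed or distance, and section 2.7.2.18 collects trip duration by GPS. So a reader should not infer that pupils with few short rides and pupils with many long rides must receive identical values. Distance is a predictor, the form of the equation is not given, and the aggregation could be a sum. Even so, the analysed unit stays ml/min, and neither a mean nor a sum of rates contains duration.
- *Condensed article.* Derivation details may sit in a fuller document. That would answer a silence, but here the article states the analysed unit twice, and it conflicts with the article's own account of PAEE.

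**Conclusion.** The point holds in this form: a primary outcome is fixed as a rate of intensity, which does not match the protocol's description of PAEE and cannot show the hypothesised increase in it.

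The 3.3–3.4-fold time ratio rests only on the protocol's speeds and applies only to trips of equal distance. The 3.3-fold range in Phase II rests on the per-protocol rule, a 5-day school week, and equal trip length and intensity. The VO2 values are illustrative and carry no weight beyond showing how the break-even works.

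**What to change.** *Phase I.* Convert VO2 and VCO2 to energy, subtract each participant's five-minute seated value, and report net kcal/min together with net kcal/km (or net kcal for a common distance). Fit the prediction equation to net energy. Rest, distance and duration are already recorded, so the cost is wording in section 2.7.1.2 and derivation code. The change must come before the equation is fitted.

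*Phase II.* Analyse net kcal per trip (predicted net rate × trip duration), summed per week over recorded trips. Section 2.7.2.2 plans heart-rate monitoring on every cycling trip, so duration should be recoverable from those recordings (an inference). The number of trips can come from the same recordings or from the PACO questionnaire, which is described only at baseline and follow-up. Keep mean VO2 and VCO2 as descriptive data.

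*Cost and limits in Phase II.* The seated recording is described only for Phase I, so netting must come through the equation. GPS distance and speed are described only for seven-day windows, so the sponsor must state how they are assigned to other trips. Missing trip recordings need a rule that separates a trip not made from a trip not recorded.
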